### Statistical analyses

The quantitative data will be monitored and analyzed by the study team and colleagues of the research group using SPSS [55]. As the statistical evaluations are carried out by the study team with the support of the biostatistician, blinding is not performed. Baseline characteristics will be compared to assessed differences of the intervention and control group, especially regarding the symptom load of secondary traumatization symptoms as well as on the presence of self-experienced traumatic events and PTSD symptoms. The effectiveness of the EMDR intervention will be assessed using a piece wise growth curve model [56], a type of the latent growth curve model, based on the assumption that change of symptomatology along the study duration is not linear but depends to certain change points. In this model, growth rates between different time periods are compared. The main criterion of interest is the symptom load of secondary traumatic stress assessed with the FST. Further parameters to be analyzed are symptom load of depression, anxiety, and somatic distress as well as professional quality of life and quality of life. For the data collected, time periods of interest are before and after the intervention for intervention group (T1–T2) and waitlist control group (T2–T3), after the intervention to follow up for both groups (intervention group T2–T3/T4, control group T3–T4), and before and after the waiting period for the control group (T1–T2). Covariates will include current psychiatric treatment, current psychopharmacological prescription or medication change, and personal traumatic experience. The data of all randomized participants who filled out the pre-and post-questionnaires and, from the intervention group, who completed at least two sessions (one preparatory session with investigation of the experiences that will be processed (phases 1–2) and at least one confrontational session (phase 3–7/8) will be included in the analysis (per-protocol analysis). Reasons for incomplete participation in the intervention will be presented descriptively. With regard to the calculation of the sample size for a piece wise growth model, there is only scarce literature on how to do so [57]. Therefore, the sample size is calculated on the basis of analysis of variance (ANOVA) with repeated measures. According to literature, EMDR shows large effect sizes (*g* = 1.01 (CI 95% 0.42 to 1.62). For the present study, however, the effect size of EMDR on secondary traumatization is not known yet. Therefore, a conservative calculation with a medium effect (*d* = 0.5) was carried out. Assuming a type I error of *α *= 0.05 and a statistical power of 0.8, a sample size of *n *= 34 is calculated [58]. Assuming a drop-out rate of 18% [59], a sample size of 40 is aimed for. Missing data will be first identified and analyzed. No further measures will be carried out in case of missing data < 5%. If > 5% of the data are missing, it will be examined whether these are related to certain variables, such for example with symptom burden and whether patterns can be recognized. If these data are missing at random, no further procedures will be carried out. If missing values are systematically related to one of the recorded variables, a multiple imputation can be performed [60]. Due to a lack existing studies, the distribution of the data cannot be estimated. Therefore, the collected data is first checked for normal distribution and if not normally distributed transformed in order to carry out the analyses with transformed data.

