## Methods/design

To answer the research question if EMDR is more effective in reducing symptoms of secondary traumatization in adult interpreters caused by their work in refugee care settings than in a waitlist-control group, a quasi-randomized controlled trial (RCT) with an EMDR intervention of three to six sessions will be conducted. Primary outcome is the symptom burden of secondary traumatic stress symptoms measured with questionnaire for Questionnaire for Secondary Traumatization (“Fragebogen zur Sekundären Traumatisierung,” FST) [31]. Secondary outcomes are symptom burden of PTSD due to self-experienced traumatic events (assessed with Posttraumatic Diagnostic Scale [32]), depression (PHQ-9 [33]), anxiety (GAD-7 [34]), and somatization (SSD-12 [35]) as well as quality of life (SF-12), quality of professional life (PROQOL-5 [36]), and psychological wellbeing (WHO-5 [37]). The study is conducted with the aim of improving trauma-informed care and, more specifically, expanding the knowledge of trauma-confrontation techniques in the broader context of trauma-related disorders, as these have repeatedly proven to be effective [38, 39].

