### Secondary outcome measure

#### Posttraumatic stress

According to current knowledge, the development of secondary traumatic stress is positively correlated with one’s own biography and the experience of traumatic event, with varying correlations [9]. For the procedure of EMDR treatment, it is important to know about traumatic events in the past and potential accompanying symptoms. Therefore, a questionnaire to assess primary traumatization (Posttraumatic Diagnostic Scale, PDS [41]) was added. The current version based on DSM-5 criteria will be used [32, 42]. The PDS-5 is a self-reporting questionnaire which measures symptoms of PTSD with 20 items on a 5-point Likert scale (0 = not at all, 4 = 6 or more times a week/severe) and is a valid and reliable measure with sensitivity of 89%, specificity of 75%, and a high internal consistency (Cronbach α = 0.92). A sum score of ≥ 36 indicates a probable diagnosis of PTSD [42].

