### Concomitant care, serious adverse events

Due to ethical considerations, participants can receive psychotherapeutic treatment or psychopharmacological medication during the study. The existence of simultaneous psychotherapy or psychopharmacological medication will be surveyed in every data collection point so that any changes in this regard are recorded. By conducting the study, no serious adverse events (SAE) are expected. Cases will be supervised regularly by an external EMDR supervisor. However, if in any case of a serious adverse event happens, this will be immediately and directly reported contact to the study team and the principal investigator. Serious adverse events include suicidal ideation, severe self-harm, or severe and ongoing exacerbation of the symptoms of secondary traumatization in the context of EMDR treatment. These will be reported systematically in non-standardized language as well as discontinuation of the study participations for other reasons. Responsible therapists will be informed about this procedure prior to the study. It will be reported by Serious Adverse Event Report Form [54]. Handling of adverse events will be decided individually. Therapeutic treatment through the outpatient clinic of the department is possible if required. A short-term increase in psychological stress is inherent in the EMDR procedure, as it is a trauma confrontation procedure. This normally subsides within a few days. This is not systematically reported as harm, as it could arise as part of the treatment, but will be discussed in the joint sessions with the responsible therapist.

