## Discussion

In this study, the effectiveness of EMDR intervention in interpreters working in refugee care who are suffering from symptoms of secondary traumatization will be evaluated. The effect on further symptomatology as well as quality of life, quality of professional life, and psychological wellbeing will be evaluated.

EMDR is an effective approach to reduce posttraumatic stress symptoms and is one of the recommended treatments for PTSD [23, 62–64]. However, the primary target of “pathological memory” that will be processed is not self-experienced traumatic events but traumatization through exposure with traumatic details of the refugee’s narratives and empathetic indirect experiencing. It is known that there is a positive correlation of having directly experienced traumatic events and of developing symptoms through secondary traumatization [9]. In a sample of interpreters working in refugee care, 58% experienced traumatic experiences themselves [17]. In EMDR treatment, potential linkages between the secondary traumatic stress and the interpreter’s potential own distressing or traumatic experiences can be activated through the reprocessing. Reprocessing potentially underlying stressful experiences is inherent in the EMDR protocol and could also affect the parameters examined. For the present study, several points of interest will be examined. Firstly, it is crucial to assess whether this type of structured and targeted treatment offer meets the needs of those affected and is subsequently utilized. Furthermore, the study aims to determine the number of sessions required to achieve a significant symptom reduction. EMDR has the potential to be an effective and time-limited intervention for the treatment of work-related secondary traumatization. If the assumption is confirmed, further studies could be carried out in other target populations affected by secondary traumatic stress. Additionally, the effect of emotional bridging to address related personal traumatic experiences will be investigated. Instead of being quantifiable, these results will be observed and stated descriptively after being seen during therapy sessions.

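### Worsening of PTSD from the interpreters' own traumatic events is not named in the serious-adverse-event definition, and the PDS-5 is absent from the analysis list although it is a declared secondary outcome

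*Protocol article*

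**What the plan says.** **Mechanism.** The Intervention section allows a session to move to earlier stressful memories through affect bridges, and to close with the disturbance rating reduced but not at zero. The Discussion says that the interpreter's "potential own distressing or traumatic experiences can be activated through the reprocessing", and that such reprocessing "is inherent in the EMDR protocol and could also affect the parameters examined". It also reports that 58% of a sample of interpreters in refugee care had traumatic experiences of their own.

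**Outcome.** Methods/design states: "Secondary outcomes are symptom burden of PTSD due to self-experienced traumatic events", measured with the PDS. The abstract says the same. The Posttraumatic stress section gives the threshold: "A sum score of ≥ 36 indicates a probable diagnosis of PTSD". The last sentence of the Quality of life section says that changes in total scores or subscales of the primary and secondary outcomes, before against after the intervention and between groups, are of interest for the analysis.

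**Analysis.** Statistical analyses makes the FST the main criterion and continues: "Further parameters to be analyzed are symptom load of depression, anxiety, and somatic distress", then professional quality of life and quality of life. PTSD symptoms appear there only in the baseline comparison, and personal traumatic experience only as a covariate.

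**Harm.** The section on concomitant care and serious adverse events says that these events include suicidal ideation, severe self-harm, or "severe and ongoing exacerbation of the symptoms of secondary traumatization" in the context of EMDR. Short-term distress is not systematically reported as harm. On the effect of bridging to own trauma, the Discussion says: "Instead of being quantifiable, these results will be observed and stated descriptively after being seen during therapy sessions".

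**The concern.** The protocol treats secondary traumatization and PTSD from self-experienced events as separate constructs, each with its own instrument (FST and PDS-5). It also says that the treatment can reach the second while aiming at the first. One would therefore expect the second construct to appear in the harm definition and in the list of analysed outcomes. It is named in neither.

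Two things are at stake. A therapist who sees lasting worsening of own-event PTSD has no named category for it and must judge whether the open-ended sentence covers it. With five therapists available, those judgements may differ. An analyst who works from the Statistical analyses section could also reasonably leave PDS-5 change out. The trial wants to say whether EMDR is acceptable as well as effective for this group. That conclusion would be weaker if deterioration in own-event PTSD were reported unevenly and not tabulated.

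**Working it through.** The plan gives no figure on this point to reproduce, so the check is mainly a comparison of sections.

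**Step 1: the harm definition against the mechanism.** There are three named items: suicidal ideation, severe self-harm, and severe and lasting worsening of secondary traumatization. Only the third concerns symptom worsening, and it names one construct. Own-event PTSD is the construct that the Intervention and Discussion sections say can be touched. Because the sentence says that serious adverse events include these items, own-event worsening is unnamed rather than excluded.

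**Step 2: the analysis list against the secondary-outcome headings.**

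| Heading under Secondary outcome measure | In the Statistical analyses list? |
|---|---|
| Posttraumatic stress (PDS-5) | No |
| Professional quality of life (PROQOL-5) | Yes |
| Depression and anxiety (PHQ-9, GAD-7) | Yes |
| Somatic distress (SSD-12) | Yes |
| Quality of life (SF-12, WHO-5) | Yes |

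Four of the five headings are carried over, and the one left out is posttraumatic stress. The abstract, Methods/design and the end of the Quality of life section all imply that PDS change is an outcome. The sections therefore conflict and need to be reconciled.

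**Step 3: would the broader statement be enough?** The sentence closing the Quality of life section covers changes in scores and comparison between groups. The growth-curve model in Statistical analyses likewise compares growth rates. Both summarise groups. A group's mean PDS-5 can fall while some of its members rise past the threshold, and neither passage asks for a count of those members. The Discussion leaves bridging to description from sessions. So adding the PDS-5 to the model resolves the conflict but does not by itself count deterioration.

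**Step 4: how many participants could be exposed.** Inputs: 58% with own traumatic experiences (Discussion, another sample) and a target of 40 (Statistical analyses). Alternating allocation gives about 40 / 2 = 20 per group.

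- Expected number overall: 0.58 × 40 = 23.2, about 23.
- Binomial SD: √(40 × 0.58 × 0.42) = √9.744 = 3.12. Range: 23.2 ± 1.96 × 3.12, about 17 to 29.
- Treated during T1-T2, intervention group only: 0.58 × 20 = 11.6, about 12.

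This range treats 58% as known exactly and as transferable to this sample, so it understates the uncertainty. It describes who has any own traumatic experience. It does not describe who has PTSD, who reaches an affect bridge, or who worsens.

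**The case against.** The case on the other side has real force on several points.

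- **PDS change is already planned.** It is a declared secondary outcome, and the Quality of life section says that changes in the secondary outcomes are of interest. This stands. A reader might infer that the plan drops the PDS-5 from analysis, and the documents do not support that. What remains is a conflict between sections. It can be argued that the list is merely shortened, since psychological wellbeing (WHO-5) is not named in it either. But WHO-5 is described under the Quality of life heading, which is in the list, whereas posttraumatic stress has its own heading, which is not.
- **The harm definition is open.** This also stands. Suicidal ideation, severe self-harm and discontinuations are reported. New psychotherapy or medication is asked about at every data collection point, and there is external supervision and a weekly team meeting. A reader might infer that no event of this kind could ever be reported. The text does not require such an exhaustive reading.
- **No individual success is defined.** A reader might infer that someone whose FST falls while own-event PTSD worsens is counted as a success with no harm on record. The plan has no responder status, and a PDS-5 rise would be in the data. The FST also draws on PTSD criteria, so the two scores may move together.
- **Activation is not called a harm.** The abstract presents reprocessing of own experiences as something that may contribute to the change in symptoms and quality of life, and the burden named in the safety section is short-term stress. Activation therefore cannot be called the single EMDR-specific risk that the protocol identifies. The point needs only that activation is stated to be possible and able to affect the outcomes.
- **The 58% is not a harm rate.** Agreed. It is used above for exposure only.

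None of this supplies a named category for own-event worsening, a consistent analysis list, or a count of participants who deteriorate.

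**Conclusion.** The point holds in a limited form and should be addressed. First, the symptom-worsening item in the serious-adverse-event definition does not name PTSD from own events, although the protocol says that own traumatic memories can be activated. Second, the analysis list omits the PDS-5, in conflict with the abstract, Methods/design and the Quality of life section. Third, nothing in the plan as published counts individuals who worsen on it.

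The size of any resulting under-reporting cannot be derived from the documents. The only available figure is possible exposure: about 23 of 40 participants (about 17 to 29), assuming that 58% carries over from another sample. The conclusion does not depend on that figure. It rests on the wording of the sections and on the protocol's own separation of the two constructs. It does not show that the harm will occur or that it would necessarily go unrecorded.

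**What to change.** 1. In the section on concomitant care and serious adverse events, extend the exacerbation item to cover symptoms of secondary traumatization or of PTSD from self-experienced events.
2. In Statistical analyses, add the PDS-5 to the further parameters, so that the list agrees with the abstract, Methods/design and the end of the Quality of life section.
3. Report, per group for T1-T2, how many participants move from below 36 to 36 or above on the PDS-5, with the number below 36 at T1 and measured at both times as the denominator. T1-T2 is the period in which one group is treated and the other waits, so the waiting group shows how often such crossings happen without treatment. The table cannot show worsening in people already at 36 or above at T1, so it complements the first change and does not replace it.

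The PDS-5 and its cut-off are already in the protocol, so no new instrument or visit is needed. The cost is two wording changes, one extra table and possibly a few more reported events.

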### Participants and recruitment

Potential participants will be recruited in a German State registration and reception center for refugees in Heidelberg (Patrick-Henry-Village). In this initial reception center, interpreters work as professionals or on a voluntary basis in various settings, such as in social or procedural advice or in the medical field, in order to include different types of workload, intensity, and forms of care for refugees [17]. In addition, further interpreters are to be recruited in other initial reception settings and from charitable organizations. They will be contacted and informed by our study team. If they are interested, they will be invited to an initial screening appointment and informed verbally and written about the procedure of the study. If they agree to participate in the study, written informed consent will be obtained. A personal evaluation to assess inclusion and exclusion criteria will be conducted by an experienced therapist of the study team. Inclusion criteria are adult participants (≥ 18 years), working on professional or voluntary basis as interpreters in the Patrick-Henry-Village or other settings that suffer from secondary traumatic stress, verified using the Questionnaire for Secondary Traumatization and reaching the cut-off-score of ≥ 65 [31]. Exclusion criteria for participation in the study are active suicidal ideation or self-harming behavior, acute substance abuse, and psychotic symptoms. For this purpose, the respective symptoms and substance use behavior are asked about in detail during the personal interview, but no standardized tool is used. The timeline of the study design is depicted in Fig. 1. Additionally, a questionnaire-based survey with a set of different questionnaires for secondary outcomes will be conducted. These data will be assessed with an online tool. The detailed SPIRIT checklist can be viewed as an enclosed document.

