### Primary outcome measure

The questionnaire-based data collection will be carried out upon the initial screening appointment (T1) for each group. For the intervention group, the second data collection point (T2) is around 6 weeks after T1, after the last session for the intervention, then 4 weeks (T3) and 8 weeks (T4) after T2. For the waitlist control group, T2 will be 6 weeks after T1, then after their last session (T3) and 4 weeks (T4) after T3. Also see Fig. 1. The participants will receive the link to the online questionnaires as well as reminders, if necessary, by email.

Secondary traumatic stress will be surveyed with the Questionnaire for Secondary Traumatization (“Fragebogen zur Sekundären Traumatisierung,” FST) [31]. This questionnaire surveys different symptoms of secondary traumatic stress based on diagnostic criteria of DSM-V for posttraumatic stress disorder, such as rumination, intrusions or nightmares, avoidance behavior, and, furthermore, cognitive or behavioral changes. The frequency of the above symptoms in the last week is assessed by 31 items on a 5-point Likert scale (1 = never, 5 = very often). From a sum score of ≥ 65, moderate secondary traumatic stress can be assumed. The structure of the questionnaire is similar to the Impact of Event Scale [40] and is designed to be used in professional context. It showed good internal consistency for the total score (Cronbach’s *α* = 0.94) in three different samples of professionals.

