#### Quality of life

Beyond the previous aspects, health-related quality of life (Short Form 12, SF-12 [48]) as well as psychological wellbeing (WHO-5 [37]) will be examined. The SF-12 questionnaire is a non-disease-specific instrument and covers 8 categories, which include questions about limitations in physical or social activities, hindrance of usual role activities due to physical or psychological problems, physical pain, general mental health, vitality, and general health perception. Two scales are used to measure physical (Physical Component Summary, PCS)) and psychological aspects (Mental Component Summary, MCS)) of health-related quality of life, which show a good internal consistency with Cronbach’s *α* = 0.89 (PCS) and *α* = 0.89 (MCS) [49, 50]. Summary scores for each scale are calculated, with an average ≥ 50 indicating a better mental or physical health than the average population and ≤ 50 indicating a worse mental or physical health than the average population. The WHO-5 is one of the most frequently used questionnaires to measure general, subjective well-being with a good internal consistency (Cronbach’s *α* = 0.80–0.92). Psychological well-being is recorded using five questions about a good mood, inner peace and relaxation, energy, ability to regenerate through sleep, and enthusiasm in the last 2 weeks. These can be agreed on a scale of 1–5 with 0 = at no time and 5 = all the time. A total score is calculated based on the number of points and multiplied by 4, with a score of 0 representing the worst and a score of 100 representing the best well-being. Used as a screening tool for depression, a sum score ≤ 50 indicates a positive screening result [37]. For the analysis of the results, the changes in the total scores or the described subscales of the primary and secondary outcomes before the intervention (T1) compared to after the intervention (T2, T3), as well as in the comparison of the intervention group with the control group, are of interest.

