
### Data collection management

Data will be collected manually at the first appointment (informed consent, Questionnaire for Secondary Traumatization, information on exclusion criteria) and then via online-survey with “Unipark” [61]. Correct and accurate data collection and, if necessary, reminding of participants will be performed manually at regular intervals. No further control of data collection will be performed. Only members of the study team and colleagues of the research group have access to the dataset. Data are stored pseudonymized in a secure and accessible manner in the responsible department. Third parties do not have access to the data.

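### The qualifying FST score is also the T1 baseline, so before–after and cross-period EMDR contrasts carry unequal regression to the mean; the unaffected concurrent T1–T2 contrast should be named as the test

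*Protocol article*

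**What the plan says.** Participants and recruitment admits interpreters whose secondary traumatic stress is "verified using the Questionnaire for Secondary Traumatization and reaching the cut-off-score of ≥ 65". Primary outcome measure sets the baseline at the same visit: "The questionnaire-based data collection will be carried out upon the initial screening appointment (T1) for each group". Data collection management confirms where the FST is taken: "Data will be collected manually at the first appointment (informed consent, Questionnaire for Secondary Traumatization, information on exclusion criteria"), with later data coming from the online survey. No second FST before treatment is described, so the qualifying score is the T1 score.

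The waitlist group's score before its own EMDR is T2: "For the waitlist control group, T2 will be 6 weeks after T1, then after their last session (T3"). The cut-off is not applied again at that point.

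Statistical analyses specifies a piecewise growth curve model and states: "In this model, growth rates between different time periods are compared". The EMDR periods are defined as follows: "time periods of interest are before and after the intervention for intervention group (T1–T2) and waitlist control group (T2–T3"). The waitlist's T1–T2 waiting period and the follow-up periods are also listed. The covariates are treatment, medication and personal trauma; T1 FST is not among them. The end of the Quality of life section names as of interest the changes "before the intervention (T1) compared to after the intervention (T2, T3"), together with the comparison between groups.

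Background and the opening of Methods/design state the hypothesis as EMDR against waitlist control.

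**The concern.** People who enter because one week's score was high will on average score lower six weeks later, treated or not. The FST asks about the last week only, so short-lived fluctuation in it is plausible. Any change measured from T1 contains that fall. A change measured from T2, where nobody was selected, contains less of it.

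The listed periods therefore do not measure the same thing. Intervention T1–T2 is EMDR plus the full fall. Waitlist T1–T2 is the full fall alone. Waitlist T2–T3 is EMDR plus whatever remains of the fall. Before–after change in the intervention group can look like efficacy when EMDR does nothing. Setting the waitlist's EMDR period against its own waiting period can hide a real effect. With 34 to 40 participants and no contrast designated as the main one, a claim could rest on a comparison whose false-positive rate is well above the 0.05 assumed in the sample-size calculation.

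**Working it through.** **The plan's own figure.** The plan gives no figure for regression to the mean. Its n = 34 reproduces as a repeated-measures ANOVA with 2 groups, 2 measurements, f = d/2 = 0.25, alpha 0.05 and a within-person correlation of 0.5 (my assumption; none is stated): N = 34, power 0.807. The within-person time factor and the group-by-time interaction both give 34, so the sample size does not reveal which contrast was meant. This point does not change the sample size.

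**Inputs.**
- Entry cut-off FST 65, and T1 at screening: from the protocol article.
- Share above the cut-off, 21%: the prevalence in Background, assumed to correspond to FST 65 or above.
- Retest correlation r over six weeks: not given. The stated Cronbach's alpha of 0.94 is taken as an upper bound, because internal consistency ignores week-to-week change; r = 0.7 is the assumed lower end.
- FST SD: not given, so results are in SDs of the unselected population, taken as normal with a stable mean and SD.
- 17 per arm: half of 34.

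**Step 1: fall from T1 to T2, present in both arms.** With 21% above it, the cut-off lies at c = 0.806 SD. Then φ(c)/P(Z ≥ c) = 1.372, and the SD of the selected T1 scores is 0.473. Expected fall = (1 − r) × 1.372.

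| r | fall, population SD | ÷ 0.473 = fall, selected-sample SD |
|---|---|---|
| 0.94 | 0.06 × 1.372 = 0.082 | 0.17 |
| 0.80 | 0.20 × 1.372 = 0.274 | 0.58 |
| 0.70 | 0.30 × 1.372 = 0.412 | 0.87 |

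**Step 2: fall from T2 to T3.** This depends on the correlation model. If correlations are exchangeable (a stable level plus short-lived noise), it is 0. Under AR(1) it is r(1 − r) × 1.372: 0.077, 0.220 and 0.288 for r = 0.94, 0.8 and 0.7, that is, a share r of the T1–T2 fall.

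**Step 3: what each contrast estimates** if the true effect is −0.50 population SD and r = 0.8.

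| Contrast | Exchangeable | AR(1) |
|---|---|---|
| Intervention T1–T2, before–after | −0.500 − 0.274 = −0.774 | −0.774 |
| Waitlist T2–T3, before–after | −0.500 | −0.500 − 0.220 = −0.720 |
| Waitlist EMDR period minus its waiting period | −0.500 + 0.274 = −0.226 | −0.720 + 0.274 = −0.446 |
| Intervention EMDR period minus waitlist EMDR period (should be 0) | −0.274 | −0.774 + 0.720 = −0.054 |
| Concurrent T1–T2, intervention minus waitlist | −0.774 + 0.274 = −0.500 | −0.500 |

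Simulation agrees with these to within about 0.002.

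**Step 4: rejection rate at nominal 5% with no EMDR effect**, 17 per arm, exchangeable correlation, simulated.

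| r | Intervention before–after | Intervention T1–T2 vs waitlist T2–T3 | Concurrent T1–T2 |
|---|---|---|---|
| 0.94 | 15% | 10% | 4.8% |
| 0.80 | 41% | 24% | 5.0% |
| 0.70 | 59% | 33% | 4.5% |

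The first column depends only on the T1–T2 correlation, so it is the same under AR(1). The second column would be lower, in line with Step 3.

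**Sensitivity.** At r = 0.8 the T1–T2 fall is 0.40 population SD if 6% lie above the cut-off and 0.16 if 50% do. At r = 0.5, with 21% above, it is 0.69.

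**The case against.** The strongest reply is that the trial's hypothesis is EMDR against waitlist, that both arms pass the same cut-off at T1, and that Statistical analyses lists the waitlist's T1–T2 period as the concurrent comparator. Regression to the mean then cancels in expectation, and the simulated error rate confirms it. This stands in full. A reader might infer that every planned comparison, or the hypothesis test itself, is biased; the documents do not support that.

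A second reply is that ranking the model's contrasts is commonly left to a statistical analysis plan. That would dispose of mere silence. Here, however, the article itself fixes the model, the periods and the principle of comparing growth rates across periods, and gives unlike periods the same label.

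Third, a reader might infer that the two EMDR slopes will be pooled or held equal, or that a paired before–after test decides efficacy. Neither is stated. The before–after error rates show what such a reading would cost; they are not the error rate of a declared primary test.

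Fourth, one cannot say that waitlist T2–T3 is free of regression to the mean. That holds under exchangeable correlation; under AR(1) much of the fall persists and the between-period bias is small.

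Finally, the size rests on assumptions. At r = 0.94, from the only reliability figure given, the fall is just 0.08 population SD. Secondary outcomes were not used for selection and regress only through their correlation with the FST; nothing here sizes that.

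**Conclusion.** The point holds in a limited form. The qualifying FST is the T1 baseline, so raw change from T1 includes regression to the mean in both arms. The intervention group's before–after change overstates EMDR, the waitlist's EMDR period minus its waiting period understates it, and the two arms' EMDR periods are not like for like. The concurrent T1–T2 contrast is not biased by this mechanism. The defect is that the plan sets the affected comparisons beside it without giving it precedence.

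The direction is firm; the size is not. Under normality, 21% above the cut-off and r from 0.94 to 0.7, the fall is 0.08 to 0.41 population SD (0.17 to 0.87 selected-sample SD), and a before–after test in 17 people rejects in about 15% to 60% of trials with no effect. For scale, the planned effect is d = 0.5, although the protocol does not say which SD that refers to. The between-period bias is largest under exchangeable correlation and much smaller under AR(1).

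**What to change.** In Statistical analyses, name the concurrent between-group difference in FST change from T1 to T2, adjusted for T1 FST, as the confirmatory EMDR contrast at alpha = 0.05. Describe the before–after changes, the comparisons between periods within an arm, and the comparison of the two arms' EMDR periods as supportive and descriptive. State there, and where the Quality of life section lists changes from T1, that such changes include regression to the mean. Add that waitlist T2–T3 is less affected but has no concurrent control.

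This changes wording only: no new visits, data or participants. The small cost is that the waitlist's later EMDR data no longer support the confirmatory claim.
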